### Statistical analyses

All primary and secondary endpoints will be analyzed on an intention-to-treat basis (all patients analyzed as part of their assigned treatment group). The endpoints will also be analyzed both on a per-patient and per-lesion basis, whenever applicable. For patients receiving multivessel PCI, the index lesion analyzed in the per-patient analysis will be determined randomly by a computer prior to QCA analysis. For intent-to-treat analysis, all patients who signed the written informed consent form and are randomized in the study will be included in the analysis sample, regardless of whether or not the correct treatment was administered, or whether crossover occurred.

The second primary endpoint of 12-month cumulative TLF and 1-month cumulative net clinical outcome will be analyzed by comparing the Kaplan-Meier event rates using the log rank test on an intention-to-treat basis. The null hypothesis will be evaluated using a non-inferiority statistics. The outcomes will also be analyzed according to subgroups defined a priori. These include the following: for comparison of the stent arm, subgroup analysis will be performed according to the lesion length, vessel size, renal dysfunction, multivessel stenting, and presence or absence of diabetes mellitus; for comparison of the antiplatelet arm, subgroup analysis will be performed according to the prescription status of calcium-channel blockers, 3-hydroxy-3-methylglutaryl-coenzyme A (HMG-CoA) reductase inhibitors, allocated stent, renal dysfunction, multivessel stenting, and the presence or absence of diabetes mellitus. The multiple imputation method will be used to handle missing data.

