## Methods

### Study objectives and hypotheses

The primary objective of the present study is to compare the efficacy and safety of coronary stenting with the PtCr-EES compared with the CoCr-ZES in the treatment of coronary stenosis, and to evaluate the efficacy and safety of a 1 month duration of TAT consisting of aspirin, clopidogrel 75 mg, and cilostazol 200 mg versus DDAT consisting of aspirin and clopidogrel 150 mg. The working hypothesis of this trial is that PtCr-EES is non-inferior to CoCr-ZES in prevention of target lesion failure (TLF) at 1-year post PCI, and TAT is non-inferior to DDAT regarding net clinical outcome, defined as a composite of cardiac death, non-fatal myocardial infarction (MI), stent thrombosis, stroke and PLATO ('PLATelet inhibition and patient Outcomes') major bleeding at 1 month [14].

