### Interventions and study device, drug

PCI will be performed with the standard technique and device, that is, catheter, guidewire and balloon catheter. The decision to predilate the lesion, use glycoprotein IIb/IIIa inhibitors and dilate the stent adjunctively will be up to the operator's discretion. The Promus Element stent is available in diameters of 2.25, 2.5, 2.75, 3.0, 3.5 and 4.0 with lengths of 8, 12, 16, 20, 24, 28, 32, and 38 mm (32 and 38 mm lengths not available for 2.25 and 2.5 mm diameters). The Endeavor Resolute stent is available in diameters of 2.5, 2.75, 3.0, 3.5 and 4.0, with lengths of 12, 15, 18, 24, 30 and 38 mm (except for 2.5 mm stents which are available as 14 mm length instead of 15 mm, and 38 mm lengths not available for 2.5 and 2.75 mm diameters). It will be recommended that all diseased coronary or graft lesions that are the targets of intervention be fully covered by the stent, with non-diseased tissue at each end of the stent. In cases of long lesions that cannot be fully covered by one stent, stent overlap of approximately 1 mm to 4 mm will be recommended per manufacturer's instruction for use (IFU). It will be recommended that the allocated stent be implanted in all lesions treated in the same patient. However, other stents may be used in case of device failure, or situations where the operator decides that it is in the best interest of the patient to do so. The use of intravascular ultrasound (IVUS) or optical coherence tomography (OCT) to guide in the procedure will also be up to the operator's discretion.

All patients will receive approximately 300 to 600 mg of clopidogrel and 300 mg of aspirin loading before the procedure. The patients randomized to the TAT group will receive an additional loading of 200 mg cilostazol (Otsuka, Korea) followed by 100 mg twice a day maintenance. Those randomized to the DDAT group will receive 150 mg of clopidogrel maintenance.

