### Outcome measures

There are two primary endpoints in this study. The primary endpoint of the trial for the stent comparison will be TLF, defined as a composite of cardiac death, target vessel-related non-fatal MI and ischemia-driven target lesion revascularization (TLR) at 12 months. The primary endpoint for the antiplatelet regimen comparison will be net clinical outcome, defined as a composite of cardiac death, non-fatal MI, stent thrombosis, stroke and PLATO major bleeding at 1 month [14]. The individual component definitions appear in Additional file 2: Appendix B. Stent thrombosis will be adjudicated according to the definitions of the Academic Research Consortium [15]. All endpoints will be analyzed principally on an intention-to-treat basis.

Secondary endpoints of the study will include all of the individual components of the primary endpoint. In addition, all death, ischemia-driven target vessel revascularization (TVR), target vessel failure (TVF), acute success (device, procedure) will be included as secondary endpoints. In the subgroup of patients that receive 13-month angiographic follow-up, both stents will also be analyzed using quantitative coronary angiography (QCA) for late luminal loss, percentage diameter stenosis, IVUS for percentage neointimal volume, or OCT for percentage neointimal coverage. In another subgroup of patients with on-treatment platelet reactivity (OPR) measurement, OPR will be compared between the two antiplatelet regimens, and according to genotype status. The effect of OPR on clinical outcome will also be analyzed.

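### Stent comparison: only intention-to-treat, with crossovers kept in, is named for a non-inferiority test although other stents are permitted; a supportive per-protocol analysis would be a cheap improvement

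*Protocol article*

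**What the plan says.** **Hypothesis.** Under Study objectives and hypotheses, the working hypothesis for the stents is that "PtCr-EES is non-inferior to CoCr-ZES in prevention of target lesion failure (TLF) at 1-year post PCI". The antiplatelet hypothesis is also non-inferiority.

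**Analysis set.** Statistical analyses states: "All primary and secondary endpoints will be analyzed on an intention-to-treat basis (all patients analyzed as part of their assigned treatment group". It then defines the set as all consenting, randomised patients, "regardless of whether or not the correct treatment was administered, or whether crossover occurred". Outcome measures is slightly softer: "All endpoints will be analyzed principally on an intention-to-treat basis". Neither section names a second analysis set. The sentence "The endpoints will also be analyzed both on a per-patient and per-lesion basis, whenever applicable" concerns the unit of analysis and does not define a per-protocol or as-treated set.

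**Stent adherence.** Interventions and study device, drug says: "It will be recommended that the allocated stent be implanted in all lesions treated in the same patient". The exception to this is worded: "other stents may be used in case of device failure, or situations where the operator decides" that switching serves the patient best. The section sets no limit on this and makes no comparable provision for switching antiplatelet regimen.

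**Blinding.** Study design describes the trial as single blind with blinded endpoint evaluation. That the operator knows the allocated stent is an inference, but a safe one, since the operator implants it.

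**The concern.** In a superiority trial, crossover makes intention-to-treat conservative. In a non-inferiority trial it works the other way: if the new device is worse, each patient who receives the other arm's stent brings the observed hazard ratio closer to 1 and makes the margin easier to meet.

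Some switching is foreseeable here. Study population sets no angiographic exclusions, and the size lists under Interventions and study device, drug differ between the stents. The PtCr-EES is listed in a 2.25 mm diameter and an 8 mm length, while the CoCr-ZES lists start at 2.5 mm and 12 mm. Some patients allocated to CoCr-ZES may therefore have lesions with no matching size of their allocated stent.

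The stated question, in Study objectives and in the Discussion, is how the two devices compare. A positive result would be harder to read as evidence about the devices if a noticeable share of patients did not receive the allocated one, and no analysis named in the article would show how much this mattered.

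**Working it through.** **Inputs from Sample size calculations.** 3,750 patients; 2:1 allocation (PtCr-EES:CoCr-ZES); 12-month target lesion failure 6.5% in each arm; margin hazard ratio (HR) 1.5; 5% attrition; one-sided α 2.5%; power at least 80%.

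**Step 1: reproduce the design figure.**
- Patients after attrition: 3,750 × 0.95 = 3,562.5. Expected events: 3,562.5 × 0.065 = 231.6.
- Information factor for 2:1 allocation: (2/3) × (1/3) = 2/9.
- Power = Φ(ln 1.5 × √(231.6 × 2/9) − 1.96) = Φ(2.909 − 1.960) = 82.9%.

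This agrees with the stated figure. The calculation allows for attrition but not for crossover.

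**Step 2: set the device effect at the margin.**
- CoCr-ZES 6.5%; PtCr-EES 1 − 0.935^1.5 = 9.59%.
- With 2,375 and 1,187.5 evaluable patients, about 305 events are expected. With no crossover, the chance of passing is 2.5% by construction.

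**Step 3: mix the arms.** Let c be the share of patients whose stenting is wholly switched. The document gives no value; 5% and 10% are assumptions. With arm rates a (PtCr-EES) and b (CoCr-ZES):
- Observed HR = ln(1 − a) / ln(1 − b)
- Chance of passing = Φ((ln 1.5 − ln HR)/SE − 1.96)
- SE is either 1/√(events × 2/9) or √(1/events in PtCr-EES arm + 1/events in CoCr-ZES arm). The ranges below span both.

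Worked case, two-way exchange, c = 10%:
- a = 0.9 × 9.59% + 0.1 × 6.5% = 9.28%
- b = 0.9 × 6.5% + 0.1 × 9.59% = 6.81%
- HR = 1.381, with 301 events
- ln 1.5 − ln 1.381 = 0.0825
- SE = 0.122 gives Φ(−1.285) = 9.9%; SE = 0.130 gives Φ(−1.325) = 9.3%

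| Switching pattern | 5% crossover: HR, chance of passing | 10% crossover: HR, chance of passing |
|---|---|---|
| Two-way between the study stents | 1.44, 5.0–5.3% | 1.38, 9.3–9.9% |
| One-way, PtCr-EES arm to CoCr-ZES | 1.475, 3.4% | 1.45, 4.5–4.6% |
| One-way, CoCr-ZES arm to PtCr-EES | 1.46, 3.8–3.9% | 1.43, 5.6–5.9% |
| Third stent in both arms, with the event risk of one or other study stent | 1.46–1.475, 3.4–3.9% | 1.43–1.45, 4.5–5.9% |

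A simulation of the two-way case gave 2.7%, 5.2% and 9.8% at c = 0, 5% and 10%, in line with the formulas.

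**Step 4: power of a per-protocol set under equal 6.5% rates.**
- 5% excluded: 220.0 events, Φ(2.835 − 1.960) = 80.9%.
- 10% excluded: 208.4 events, Φ(2.759 − 1.960) = 78.8%.

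**The case against.** **The article is condensed.** A full protocol or analysis plan, not shown, may name a per-protocol set, and Outcome measures says intention-to-treat is used principally, not exclusively. This stands as a limit: one cannot say that the trial rests on intention-to-treat alone, only that this document names nothing else. The point survives because the article does more than stay silent. It foresees crossover and fixes how it is handled.

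**Intention-to-treat is a proper analysis.** For the effect of being assigned to a stent, the error rate remains 2.5%. This stands. The excess applies only to a conclusion about the device received, and only if crossover occurs.

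**Switching is not free.** The allocated stent is recommended and two exceptions are named. This stands, although the best-interest exception is broad. Also, the other stent need not be the comparator, and a patient with several lesions may have only one switched. The two-way figures are therefore the upper end of the patterns examined.

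**A reader might infer that both non-inferiority claims are affected.** The document does not support that. The switching clause concerns stents, and in a factorial design a change of stent does not bring the two antiplatelet regimens together. A false-positive rate for that comparison would rest on a regimen crossover that the article does not describe.

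**Per-protocol analysis has its own bias.** Switching is likely to depend on lesion difficulty, so the bias could run either way. This stands, and it argues for a supporting role. Requiring the margin to be met in both sets is a debatable convention; with 10% excluded, per-protocol power alone is already below the stated 80%.

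**Conclusion.** The point holds for the stent comparison, as an inexpensive improvement and not as an error in the planned test. The article combines a non-inferiority hypothesis, a single named analysis set that keeps crossovers, and permission to implant other stents without a stated limit.

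At a true device hazard ratio of 1.5, 5% crossover would move the chance of declaring non-inferiority from 2.5% to between 3.4% and 5.3%, and 10% to between 4.5% and 9.9%. These figures assume the crossover rate, whole-patient switching, a 6.5% rate with CoCr-ZES and, for a third stent, an event risk equal to that of one or other study stent. If little switching occurred, the effect is small. The article gives no basis for choosing among these cases, which is why crossover should be reported.

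**What to change.** Keep intention-to-treat as the primary analysis. Add to Statistical analyses:

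1. A pre-specified supportive per-protocol analysis of 12-month target lesion failure at the same HR 1.5 margin, in patients whose treated lesions all received only the allocated stent.
2. A report, by arm, of how many patients received a stent other than the one allocated, separating the other study stent from a third stent.
3. A statement that a non-inferiority conclusion will be qualified if the two analyses disagree.

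Trial status says that recruitment is complete and follow-up continues, so this can be fixed in writing before the analysis. It needs only a record of which stent went into each treated lesion, which the planned per-lesion analyses suggest is available.

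The cost is one further analysis, in a set that is not fully randomised and has slightly less power (80.9% with 5% excluded, 78.8% with 10%, against 82.9%). It should therefore support the intention-to-treat result and not replace it. A matching analysis may be run for the antiplatelet comparison, but nothing in the article makes it necessary.

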### Trial organization and ethical considerations

The overall trial organization is summarized in Additional file 2: Appendix C. The trial was designed by the principal investigators and the executive committee. Besides the executive committee, the steering committee, data safety monitoring board, and the clinical event adjudication committee will be involved in the execution, administration, and supervision of the trial. The specific role and information regarding each of the committees appear in Additional file 2: Appendix C. The study will be sponsored by the Seoul National University Hospital (SNUH) Cardiovascular Clinical Research Center (CCRC) and the data will be managed by an independent contract research organization, Dream CIS Inc. Dream CIS will be responsible for the development of a web-based randomization system, maintenance of the web-based case report form, and data collection from individual sites. Site monitoring will be performed by the CCRC of SNUH. The trial monitors will review the documents of at least 30% of the patients enrolled from each participating center, at appropriate intervals, for accuracy and completeness and to ensure compliance with the protocol. The trial monitor will be able to inspect all documents and required records that are maintained by the individual investigator and site, including medical records (office, clinic, or hospital) for the subjects in this trial. The study will be performed in accordance with the Declaration of Helsinki. Before participation of the study, each patient will be given full information, that is, purpose, methods, rights, duties and possible risk/benefits of the study in plain, lay language. Written, informed consent is a prerequisite to the participation in the study.

### Ethical approval

This study was approved by the institutional review board at Seoul National University Hospital (D-1005-001-068) and by the local ethical committee at each participating hospital. The protocol of the trial has been registered at http://www.clinicaltrials.gov (NCT01267734).

## Discussion

### EES and ZES in clinical practice

The second-generation CoCr-EES (Xience V, Promus) has been shown to be either comparable or better than its first-generation counterparts. In large scale randomized trials against paclitaxel-eluting stents (PES), such as the SPIRIT IV and COMPARE trials, it was superior to PES with regard to both efficacy and safety where the primary clinical endpoints were reduced by 38% and 31%, respectively [1,2], which has now been reaffirmed in a meta-analysis [16]. In randomized trials and meta-analysis comparing CoCr-EES and SES, such as the EXCELLENT, ISAR-TEST 4, SORT-OUT IV, and so on, CoCr-EES showed similar efficacy with slight trend toward superior safety [4-6]. The next addition to the second-generation DES market has been the CoCr-ZES (Endeavor Resolute), which showed equivalent outcome compared with the CoCr-EES in the RESOLUTE All-Comers randomized trial [7]. Because of the all-comers population that was studied in this trial, data were available regarding to the performance of the second-generation stents in complex lesions such as coronary total occlusions, bifurcation lesions, saphenous vein grafts, in-stent restenosis, unprotected left main lesions, multivessel stenting, and so on, which constituted approximately two-thirds of the lesions treated in the trial [17]. In this complex subgroup, there were no significant differences between the two DES devices but the TLF rate at 1 year numerically favored CoCr-ZES. Both of these second-generation DES are based on a cobalt chromium alloy stent. Most recently, a newly developed stent alloy, the platinum chromium alloy, was incorporated with everolimus to create the PtCr-EES, the Promus Element stent (Boston Scientific). In the only randomized trial to date with the PtCr-EES, the PLATINUM trial, where it was compared against CoCr-EES in a select group of patients with various angiographic exclusions [8], PtCr-EES was non-inferior to CoCr-EES for the primary endpoint of TLF, with insignificant differences in measures of safety and efficacy through 1 year. Both stents showed low event rates at 1 year (TLF rate: 3.4% vs 2.9% for PtCr-EES vs CoCr-EES, *P *= 0.60). However the PtCr-EES has not been studied randomly in a broader population of patients as was enrolled in the RESOLUTE All-Comers trial, which better reflects the day-to-day clinical practice in most centers of coronary intervention. The non-inferiority margin of 3.25% may seem large given that the estimated rate of the primary endpoint is 6.5%. However, in the RESOLUTE All-Comers trial and the PLATINUM trial, well known previous studies incorporating the non-inferiority design regarding stent comparisons, a non-inferiority margin of 3.5% has been used [7,8]. In addition, because of the paucity of the data on PtCr-EES, the sampling ratio was set at 2:1 to maximize the number of patients randomized to the PtCr-EES arm.

### Antiplatelet regimen after PCI

Antiplatelet therapy is one of the most important components of successful outcome after PCI. High on-treatment platelet reactivity (HOPR) has been shown to be an independent predictor of thrombotic outcomes [9-12]. In particular, the first month after PCI is the most important period to inhibit platelet function to prevent thrombotic events, since the greatest association between heightened platelet reactivity and thrombotic outcome is seen in the first month post PCI [18]. In Korea, where the HOPR rate of the general population receiving PCI is above 50% and frequency of the cytochrome P450 2C19 (CYP2C19) loss-of-function (LOF) allele is greater than 60% [12,19-21], we may need increased platelet inhibition during this critical period.

To increase platelet inhibition after PCI, the approach is slightly different between Western and Asian doctors. Before prasugrel and ticagrelor, most Western doctors prescribed double dose of clopidogrel in high-risk settings. However, in Asia and in particular in Korea, doctors prefer addition of cilostazol on conventional dual antiplatelet therapy (DAPT) to doubling the dose of clopidogrel. In the CURRENT-OASIS 7 trial, a 1-week duration of doubling the dose of clopidogrel was shown to improve outcome at 1 month compared with conventional dose in ACS patients undergoing PCI [13]. The basis of adding cilostazol in Korea comes from pharmacodynamic studies from our group and others, which have shown that TAT is superior to DDAT with regard to inhibition of platelet reactivity in patients with high platelet reactivity [22], and in carriers of the CYP2C19 LOF allele [23]. In the DECLARE-Diabetes, and DECLARE-Long studies, TAT was superior to conventional DAPT regarding inhibition of neointima formation and significantly reduced rates of clinically driven TLR [24,25]. In the CILON-T trial, which was underpowered to show differences in clinical outcome, there were no significant difference between TAT and conventional DAPT although TAT more profoundly reduced OPR [26]. However in the *post hoc *analysis, we showed that there was a significant trend toward worse outcome in those with high OPR suggesting that cilostazol may have some beneficial effects in higher-risk populations.

Because of the paucity of sound clinical data regarding the use of TAT based on randomized clinical trials, and in light of the abundant use of cilostazol as a third agent in post-PCI management in Korea, a large scale randomized controlled trial (RCT) to confirm the safety and efficacy of TAT is needed at present. After initiation of the 'Harmonizing Optimal Strategy for Treatment of coronary artery stenosis - sAfety & effectiveneSS of drug-elUting stents & antiplatelet REgimen' (HOST-ASSURE) trial, we anticipate enrollment within 1 year. The large scale and all-comers design of the HOST-ASSURE trial will provide important insight into two issues in interventional cardiology. First, it will test whether the newest DES platform, PtCr-EES will be as effective and safe as CoCr-ZES in preventing TLF. Second, it will also address the issue of whether TAT is non-inferior to DDAT in reducing net clinical outcome within the first month post PCI.

### Trial status

The HOST-ASSURE Trial is ongoing. Patient recruitment has been completed and follow-up is being conducted.
